Women of reproductive age have a lactobacillus-dominant flora and an acidic vaginal pH (<4.5), in contrast to pre-menarchal and post-menopausal females where the vaginal flora predominantly consists of anaerobic rods and cocci and vaginal pH is more alkaline (>4.5). The vaginal microflora of women is directly related to oestrogen levels [4]. Oestrogen increases deposition of glycogen in vaginal epithelial cells and glycogen is a substrate for Lactobacillus spp, which generate lactic acid from glucose [4]. Lactic acid has been shown to be a potent inhibitor of BV-associated organisms [35]. Cross-sectional studies, including our own, have also shown that the use of hormonal contraception is associated with a lower risk of BV [35-37]. Our recent cohort study provided the only published prospective data indicating that hormonal contraception may be associated with a lower risk of recurrent BV [18].  Topical vaginal oestrogen preparations are commonly used in post-menopausal women and oestrogen-deficient states to improve vaginal dryness, they are well tolerated and minimal systemic absorption occurs so that they are safe in conditions where oral oestrogen preparations are contraindicated. We anticipate an added benefit from the inclusion of oestriol in Gynoflor on the vaginal pH and flora.
Public health implications of BV
BV is common and is associated with significant sequelae. Perhaps the two greatest areas of public health significance are its association with adverse pregnancy outcomes, specifically preterm delivery, and its association with increased transmission of HIV. In addition, as the most common cause of abnormal vaginal discharge, significant time and health resources are spent in diagnosis and treatment of this condition. While current treatment regimens have poor efficacy, it will be difficult to achieve significant reductions in BV-associated sequelae, and considerable clinical resources are consumed by repeated presentations of women with BV recurrence to medical services. If more than half of treated women have experienced BV recurrence within a year of recommended therapy, clearly there is a need to investigate alternative more effective approaches to the management of this common condition.
RESEARCH PLAN
Aims 

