All participants will have a clinical history taken and undergo speculum vaginal examination, including pH estimation (Spezialindikator strips pH 2-9, Merck & Co., NJ, USA).  After explanation of the trial, women will be invited to participate and to provide written informed consent. Participants will then be asked to complete a questionnaire (regarding behavioural practices, risk factors for STIs, symptomatology {rating scale 1-5}, previous BV episodes and prior treatments). The clinicians will complete a pre-formatted data collection sheet on examination findings (e.g. presence of discharge, nature of discharge), genital specimens will be collected for vaginal microscopy, Chlamydia trachomatis PCR, Neisseria gonorrhoeae culture, and Trichomonas vaginalis culture, and a separate vaginal swab will be stored at -70oC for later analysis.  Following randomisation, study medication will be dispensed as outlined.  

Follow up at 4, 8 weeks, 12 weeks and 6 months
Kits containing a questionnaire, vaginal swab, glass slide, instructions for self-collection, and a prepaid envelope, will be used to examine BV recurrence and factors associated with recurrence at 4, 8 weeks, 12 weeks and 6 months following treatment. The first kit for the 4 week follow-up will be given to participants at the enrolment visit, at which point clear verbal and written instructions will be also be provided and participants given the opportunity to clarify any concerns. Kits for follow-up at 8, 12 weeks and 6 months will be posted to participants. At each follow-up point, participants will be asked about sexual and contraceptive practices, genital symptoms, oral and vaginal self-treatments, and clinician-prescribed therapies. They will self-collect a vaginal swab and make a smear on a glass slide, and return the swab, slide and questionnaire in the prepaid envelope (18). Reminders in the form of telephone calls, letters or SMS text-messages will be sent once she has received the kit by post and weekly after the due date for four weeks. If no specimens are received by this time, the woman will be classified as a non-responder for that interval. Non-responders will still be contacted at the subsequent follow-up point(s). 

Interval BV symptoms and unscheduled visits

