Women will receive a card and refrigerator magnet with the free call study telephone number, which will be staffed by the study nurse and research investigators. Participants will be encouraged to call the number if they have symptoms of BV during the study or concerns regarding treatment or possible side effects. A sample kit will be supplied to women so that if they are unable to attend MSHC they will be able to self-collect samples for interval symptoms after discussion with the research nurse. Women will be asked in the initial consenting process to allow any results from outside clinics for investigation of BV symptoms to be made available for the study. 

These procedures are similar to those we have previously used in the study of BV recurrence (18,36) and the trial of probiotics for vaginal candidiasis (38).  Only 3/130 and 3/287 women attended outside clinics in these studies as a result of providing easy and rapid review if a woman developed interval symptoms.

Stored samples
With participant consent, vaginal swabs will be stored at -80oC for future examination for potential pathogens. DNA will be extracted using the Magnapure system: MagnaPure LC (Roche Molecular System, Alameda, CA, USA) in accordance with manufacturer's protocol, followed by detection of potential pathogens using molecular amplification technology. 

Study Outcome Measures
Primary outcome measure
Recurrence of BV within 6 months will be defined as a Nugent score of 7-10. We have chosen 6 months rather than 12 months, based on our experience of relapse rates in our previous studies of BV (Figure1). Relapse of BV plateaus by 6 months. Additionally, compliance with follow up will be higher with a 6 month compared to 12 month follow up. 

Secondary outcome measures
1.	Recurrence of abnormal flora within 6 months will be defined by a Nugent score 4-10. 
2.	Behavioural practices and other factors (eg contraceptive use, past history of BV, smoking)  associated with BV recurrence.

Validation of primary outcome
All slides will be stored and re-scored by two independent experienced microbiologists blinded to the intervention group of the participant.  If slides vary in their Nugent score groupings (0-3, 4-6 and 7-10), our experienced laboratory staff will reach consensus using methods from our previous studies of BV recurrence (18, 36). 

Sample size calculation

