The Melbourne Sexual Health Centre (MSHC) is the largest sexual health service in Victoria, and diagnoses 450 cases of symptomatic BV annually.  We estimate a BV recurrence of 50% in study arm 3 (placebo).  A sample size of 123 will be required in each group to detect a 20% difference in recurrence rates (recurrence rate of 30%) between study arm 1 or study arm 2 and study arm 3 with a power of 90% and an alpha of 0.05. Assuming a loss to follow up rate of 20%, 150 women will be recruited in each group. This would involve recruiting 50% of eligible women at MSHC which is consistent with previous studies given a research nurse will be on site to assist.

Evidence of past successful recruitment
Our team has previously successfully recruited women into similar trials.  In a cohort study of BV, we recruited 157 women from MSHC with BV in 12 months despite more restrictive inclusion criteria and no research nurse available to assist with recruitment (18, 36).  Investigators have conducted a 2 year treatment trial of BV (n=130), in which women were followed at regular intervals over 12 months using self-collected sampling in the same manner proposed for this trial. Loss to follow up over 12 months was less than 20% (18, 36). 

Data analysis
Data will be cleaned and entered into an Access database.  Analyses will be intention-to-treat.  Kaplan Meier methods will be used to generate survival curves for time until recurrence of BV and abnormal flora.  Recurrence rates and their 95%CI will be calculated.  Behavioural factors associated with recurrence of BV and abnormal flora will be investigated using a discrete time version of the proportional hazards regression model as proposed by Carlin and colleagues (38). Rate ratios and robust standard errors will be calculated using this methodology.
Randomisation
Sequence generation
Women who provide written informed consent will be randomly assigned using a computer-generated sequence to one of the three study arms. An independent MSHC researcher, with no other input into this trial, will generate and hold the random number sequence. Randomisation will occur in blocks of 15 to ensure that the allocation of women to the three arms occurs at a similar rate over the recruitment period.

Allocation concealment

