Major anticipated confounding factors and how these will be handled
By measuring all known factors that can influence the development and recurrence of BV at baseline, and ensuring an adequate sample size, this RCT should be able to account for all known and unknown confounders.

Details of contingencies:
Participants will be counselled at recruitment regarding the potential side effects of all medications being used. This verbal information will be reinforced with written information about possible side-effect and how to manage them. All participants will be provided with a card which lists the free study telephone number to call during office hours and will connect to an investigators' mobile number after hours. Finally, participants will be informed to stop using any study medications that they feel may be causing an adverse event, if they are unable to contact a researcher to discuss. 

Details of handling of adverse events:
Serious adverse events with any of the study medications are extremely unlikely, as all medicines being tested have histories of safe usage, including Gynoflor , which is available over-the-counter in Europe. For this reason, a data monitoring and safety committee will not be formed for this study. Anticipated side effects from the antibiotics are likely to be mild and to include symptoms such as nausea, headache, heartburn, diarrhoea, vaginal discharge or a metallic taste. Side-effects of Gynoflor include local irritation and burning, and vaginal discharge.  Any serious adverse event is very unlikely; however, as stated above all participants will be given clear printed instructions on a card with 9am to 9pm daily contact details. Women will be provided with their results by study investigators and if treatment of BV is required during follow-up prompt review will be arranged with a sexual health physician at Melbourne Sexual Health Centre. All clinicians at this service are highly experienced in the management of BV. Serious adverse or unforeseen events will be managed by referral of the participant to the appropriate professional for assessment and management and will be reported to the relevant ethics committee, VMIA (Victorian Managed Insurance Authority) and the TGA.

Details of methods to ensure confidential handling and storage of records:

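### The protocol credits baseline measurement and sample size with handling all confounders, but does not say that measured baseline factors enter the arm comparison

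*Protocol*

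**What the plan says.** Under *Major anticipated confounding factors and how these will be handled*, the protocol says that, by measuring all factors known to influence BV at baseline and "ensuring an adequate sample size, this RCT should be able to account for all known and unknown confounders". It offers no other handling there and refers to no other document.

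The *Data analysis* section specifies intention-to-treat analysis. For the outcome, "Kaplan Meier methods will be used to generate survival curves for time until recurrence of BV and abnormal flora", and recurrence rates with 95% confidence intervals will be calculated. It names one regression model: "Behavioural factors associated with recurrence of BV and abnormal flora will be investigated using a discrete time version of the proportional hazards regression model", giving rate ratios with robust standard errors. It does not list the model's terms, and it does not say how the arms will be compared or whether that comparison will be adjusted.

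Randomisation is 1:1:1 in blocks of 15, with no stratification factor stated.

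The prognostic factors appear in several places. *Secondary outcome measures* gives contraceptive use, past BV and smoking as examples of factors to be studied. The oestrogen rationale cites the team's own cohort as indicating that "hormonal contraception may be associated with a lower risk of recurrent BV". The enrolment questionnaire under *Visit procedures* covers "previous BV episodes and prior treatments", among other items. The Nugent score is known at entry because eligibility depends on it.

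**The concern.** The section promises a way of handling confounders, and neither step it names can do so. Measuring a factor adjusts nothing. A larger sample makes chance imbalances smaller but does not remove them, and measurement cannot reach unknown factors. Randomisation does the work that the sentence assigns to measurement, and it does so only on average.

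The baseline data are also not linked to the question the trial was sized for. The one model that could carry them is described only for the behavioural factors. If they are not used, a chance difference between arms in a strong predictor stays in the estimated effect, and the outcome variation that predictor explains stays in the error. Without a list fixed in advance, covariates could also be chosen after the results are seen.

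**Working it through.** **1. Does anything else in the protocol carry out the promise?** Randomisation is blocked, but no stratification is stated. The outcome analysis is Kaplan-Meier curves and recurrence rates. The regression is described for behavioural factors, with no mention of arm. The list of bias sources says that follow-up and intention-to-treat analysis guard against baseline imbalance; these preserve what randomisation achieved but adjust for nothing. No stated step uses a baseline factor in the arm comparison, and none is ruled out.

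**2. Reproduce the stated sample size.** Inputs from *Sample size calculation*: 50% recurrence on placebo, and enough women to "detect a 20% difference in recurrence rates (recurrence rate of 30%) between study arm 1 or study arm 2 and study arm 3", with 90% power and alpha 0.05. For the two-sided pooled formula without continuity correction, p̄ = 0.40:

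n = [1.960 × √(2 × 0.40 × 0.60) + 1.282 × √(0.25 + 0.21)]² / 0.20² = 124.0

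This matches the stated 123 to within one woman. The formula has no covariate term, so the planned power assumed no gain from adjustment.

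**3. Unadjusted power.** Power = Φ{[0.20√n − 1.960√0.48] / √0.46}.
- n = 123: (2.218 − 1.358) / 0.678 = 1.268, so power is 89.8%.
- n = 120 (150 recruited less 20%): (2.191 − 1.358) / 0.678 = 1.228, so power is 89.0%.

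**4. Possible gain from adjustment.** If baseline factors explain a share R² of outcome variance within arms, the effective size is approximately n/(1 − R²). R² is not in the documents, so a range is assumed. The half-width is for the 95% interval of the risk difference, 1.96√[0.46(1 − R²)/123].

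| Assumed R² | Power, n = 123 | Power, n = 120 | Half-width, n = 123 (points) |
|---|---|---|---|
| 0 | 89.8% | 89.0% | 12.0 |
| 0.02 | 90.4% | 89.6% | 11.9 |
| 0.05 | 91.2% | 90.5% | 11.7 |
| 0.10 | 92.6% | 92.0% | 11.4 |
| 0.15 | 93.9% | 93.3% | 11.1 |
| 0.20 | 95.1% | 94.6% | 10.7 |

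For scale, one binary factor of prevalence q with risks p₀ and p₁ around an overall 50% gives R² = q(1 − q)(p₁ − p₀)²/0.25. At q = 0.5 and an odds ratio of 2, the risks are 0.414 and 0.586 and R² is 0.029. At 30% to 50% prevalence, odds ratios of 1.5, 2 and 3 give about 0.01, 0.02 to 0.03, and 0.06 to 0.07. Three independent factors with odds ratio 2 would therefore give roughly 3 × 0.029 = 0.09; an R² of 0.20 needs about three with odds ratio 3.

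**5. Cross-check by simulation.** Assumptions: complementary log-log discrete-time model, four intervals, 150 per arm, 20% dropout, three baseline factors at 50% prevalence, 50% v 30% recurrence. Results are from 3,000 trials per scenario, with a separate run of 1,500 in brackets.
- Hazard ratios 1.5, 1.5 and 0.67: power 93.4% to 94.4% (93.1% to 93.3%).
- Hazard ratios 2, 2 and 0.5: power 93.2% to 96.7% (92.5% to 95.7%).

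**6. Chance imbalance.** For one factor at 50% prevalence and 150 per arm, the standard deviation of the difference is √(0.25 × 2/150) = 5.8 points. The chance of a difference of 10 points or more is 2[1 − Φ(1.73)] = 8%. For a factor with hazard ratio 2 and overall risk 50%, the two survival probabilities x and x² satisfy x + x² = 1, so x = 0.618 and the risks are 38.2% and 61.8%. A 10-point imbalance then moves the apparent difference by 0.10 × (61.8 − 38.2) = 2.4 points. That is 12% of the 20-point target, against an interval half-width of 12 points.

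**The case against.** The strongest reply is that the protocol is silent on adjustment and has not decided against it. The covariate list and comparison model are commonly left to an SAP, which is not shown here. A reader might infer that the arm comparison will be unadjusted, or that the regression has no arm term. The text supports neither: it does not describe the comparison and does not list the model's terms. This part of the objection stands.

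A reader might also infer that the comparison is confounded. It is not. Randomisation makes the unadjusted comparison unbiased, and its confidence interval and type I error already allow for chance imbalance. Unstratified randomisation with an unadjusted analysis is an accepted design. The sentence does refer to the trial as an RCT, so a generous reader may take randomisation as implied.

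The protocol's evidence on the factors is limited too. It lists them for investigation and says only that hormonal contraception may matter. Its enrolment procedures name previous BV episodes but neither smoking nor contraception; contraceptive practices are named at follow-up.

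The objection does not rescue the sentence itself. The section sets out to say how confounders will be handled, gives a method that cannot work, and defers to no other document. That is a misstatement, not a detail left for later.

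**Conclusion.** The statement on confounders is wrong and should be corrected, and the protocol should say whether enrolment factors enter the arm comparison. Severity is minor.

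The issue is precision and chance imbalance, not bias. It would be tempting to say that precision already paid for is lost, or that the trial falls short of its planned power. The documents do not support that, because the sample size never counted on adjustment.

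Over assumed R² of 0.02 to 0.20, the gain at 123 per group is about 0.6 to 5.3 power points; up to R² of 0.10 it is at most 2.8. These figures rest on assumed prognostic strength and on the n/(1 − R²) approximation. The 50% prevalence used for imbalance and in the simulation is the value that makes absolute imbalance largest.

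**What to change.** 1. Reword the confounding section to say that randomisation balances known and unknown factors on average, and that the arm comparisons will be adjusted for pre-specified baseline prognostic factors.
2. In *Data analysis*, state that clindamycin versus placebo and Gynoflor versus placebo will each be estimated from the discrete-time proportional hazards model already planned, with arm, interval and a short covariate list fixed before unblinding. Use enrolment values only: previous BV episodes and baseline Nugent category, plus hormonal contraception and smoking if these are recorded at enrolment.
3. Report a standardised six-month risk difference from that model, on the scale used for sizing, beside the unadjusted Kaplan-Meier estimates.
4. Keep behaviours measured during follow-up out of the arm comparison, because they come after randomisation and treatment may change them.
5. Include arm in the behavioural-factor model.

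If an SAP already fixes the covariates, items 2 to 5 can be met by a reference to it; item 1 is needed either way. The cost is a few sentences, with no extra women or visits. The one downside is that the adjusted rate ratio is conditional on the covariates and so is not directly comparable with an unadjusted one, which is why item 3 is needed.
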